## Abstract

One of the most common concerns of patients undergoing surgery is preoperative anxiety, with a prevalence of up to 48%. The effects of preoperative anxiety continue beyond the preoperative period and are associated with more severe postoperative pain and poorer treatment outcomes. Treatment options for preoperative anxiety are often limited as sedatives cause side effects and their efficacy remains controversial. Placebo research has shown that optimization of positive treatment expectations, as can be achieved through placebo administration and education, has clinically relevant effects on preoperative anxiety, pain and treatment outcomes. As the administration of masked placebos raises ethical questions, clinical studies have increasingly focused on the use of open, non-deceptive placebo administration (open-label placebo, OLP). The use of OLPs to reduce preoperative anxiety and modify clinically relevant postoperative outcomes has not yet been investigated. This bicentric, prospective, randomized-controlled clinical trial (PATE Trial; German Registry for Clinical Studies DRKS00033221), an associated project of the Collaborative Research Center (CRC) 289 “Treatment Expectation”, aims to alleviate preoperative anxiety by optimizing positive treatment expectations facilitated by OLP. Furthermore, this study examines a potential enhancement of these effects through aspects of observational learning, operationalized by a positive expectation-enhancing video. In addition, patient’s perspective on the self-efficacy and appropriateness of OLPs prior to surgery will be assessed. To achieve these objectives, female patients will be randomized into three groups before undergoing gynecological laparoscopic surgery. One group receives the OLP with a positive rationale conveyed by a study physician. A second group receives the same intervention, OLP administration and rationale provided by a physician, and additionally watches a video on OLP presenting a satisfied patient. A third group receives standard treatment as usual (TAU). Outcome measures will be effects on preoperative anxiety and postoperative experience, particularly visceral and somatic postoperative pain. As the non-deceptive administration of placebos; when indicated; may yield positive outcomes without side effects, and as current treatment of preoperative anxiety is limited, evidence from clinical placebo research has the potential to improve outcomes and patient experience in the surgical setting.

## Introduction

1

Preoperative anxiety is a very common burden for patients before surgery, with a prevalence of up to 48% (1–3). Up to 318 million surgeries were performed worldwide in 2012, with increasing global volume (4) potentially leading to over 160 million patients being affected by anxiety in the perioperative setting. Preoperative anxiety and the associated psychological stress burden manifests in increased anesthesia requirements (5) and subsequent consequences such as haemodynamic instability, impaired postoperative cognitive and physical recovery (6), prolonged recovery time and prolonged hospital stay (7). In addition, the effects persists after surgery, leading to increased postoperative pain (8, 9), which is a crucial risk factor for persistent postoperative pain (10). Moreover, higher preoperative anxiety is associated with increased opioid postoperative consumption (11) and a lower quality of life after surgery (8, 9). Also, preoperative anxiety appears to be predictor of the occurrence and level of postoperative anxiety (12). Consequently, perioperative anxiety incorporates the anxiety that occurs both before and after a surgical procedure.

Female gender and gynecological surgery are associated with more prevalent and severe preoperative anxiety (13), making this patient group of particular interest. Reducing preoperative anxiety can improve surgical outcomes, shorten hospital stay and reduce negative impact on quality of life, calling for interventions aimed at improving preoperative anxiety. Current treatment regimens are mostly based on pharmacological interventions with unfavorable side effects (14), resulting in a decrease in prescriptions (3, 6). Therefore, anesthesiologists have a crucial responsibility in guiding patients through the process between preoperative anxiety, the anesthetic as well as surgical procedure, limited treatment options and uncertain treatment success.

Placebo research already provides convincing evidence that psychological preparation for surgery has a positive effect on postoperative pain and the length of hospital stay (15). Experimental and clinical studies reveal clinically relevant treatment effects on anxiety or pain elicited by positive treatment expectations, for example by placebo pills or placebo interventions (2, 16–19). Negative expectation effects modulated by anxiety, demonstrably shape treatment outcomes, including patient-reported pain and treatment outcome (20–22). In addition, abdominal surgery can cause visceral pain, deep in the abdomen, and superficial somatic pain (23), and especially visceral pain is substantially amplified by negative emotions and cognitions, such as fear (24) or stress (25).

Placebo treatments without deception, known as open-label placebo (“OLP”), meaning patients know and agree that they are receiving a placebo, can also produce positive treatment effects (26–29). A meta-analysis of OLPs in patients with back pain, cancer-related fatigue, attention-deficit hyperactivity disorder, allergic rhinitis, major depression, irritable bowel syndrome, and menopausal hot flushes found an overall significant, moderate-sized effect of OLPs in these eleven RCTs. Such effects also include reducing test anxiety and improving self-management skills like coping, self-efficacy, introspection, hope, and self verbalization (30). Beyond that, taking OLPs alleviated pain after their administration and reduced the need for analgesics after surgery (31, 32). Positive and negative expectancy effects on treatment outcome also include placebo hypoalgesia, which refers to a reduction in perceived pain due to the psychological effects of receiving a placebo believed to be an analgesic (33), and have great potential for use in clinical settings.

Several mechanisms are currently recognized as underlying expectancy effects: Verbal information or instruction provided by healthcare professionals (cognitive model), classical conditioning (associative learning) and social learning (observational learning) (16), which generate the expectation-mediated placebo effect (34). The specific mechanisms underlying the effects of OLPs are not yet fully understood (35). However, there is evidence that these mechanisms are similar to those of deceptive placebo. When OLPs are used as an adjunctive treatment, the effect may rely on placebo responses induced by classical conditioning (36). Also, the effects of OLPs are often elicited by verbal suggestion, highlighting the important role of doctor–patient interaction and cognitive processing in the efficacy of OLP. In contrast to deceptive placebos, OLP treatments do not require patients to be blinded and promote awareness of the treatment, thereby enhancing autonomy and potentially activating the body’s self-regulatory mechanisms through conditioned responses (37). Furthermore, it is hypothesized that the success of OLP treatments is highly dependent on the active participation of the patient, whereby the recognition of the placebo (“the pill is without medication but not without effect”) may require cognitive flexibility to effectively reconcile the paradoxical information (38). Another theoretical framework for OLPs is the “Bayesian brain” model, which suggests that OLP helps to resolve cognitive dissonance by adjusting expectations based on new evidence (39). Given the limited knowledge of the mechanisms, the patients’ perspective on this novel treatment is of particular interest for the future understanding.

Treatment expectations can also arise from previous treatment experiences, as well as information from the media or peers. Our research group has investigated the modulation of expectations by verbal instructions and conditioning in experimental human and patient studies (17, 21, 32, 40, 41), but mainly experimental studies on observational learning in placebo or nocebo treatment have been conducted (33). However, we have also begun to investigate observational learning in patient populations. We were able to provide evidence that clinically meaningful effects can be achieved by patients observing placebo effects in an actor patient and changing expectations in chronic pain patients (42). Therefore, the encouraging benefits of observational learning derived from preclinical research provide an incentive to further investigate the role of observational learning as an important objective of our clinical trial concept and design in this patient population.

Reducing anxiety in the preoperative period is of utmost importance in order to reduce the risk of perioperative complications and ultimately postoperative pain after surgery. Treatment expectations have not yet been systematically studied, although a refined assessment of positive and negative expectations may complement other psychosocial risk factors in determining individual risk for adverse health outcomes, e.g. based on concern of adverse events or low self-efficacy expectations regarding the ability to cope with preoperative anxiety and postoperative pain. More importantly, it appears that expectations can be optimized. The aim of this project is to increase knowledge regarding how treatment expectations and related mechanisms can be specifically improved in a clinical context in order to improve treatment outcomes.

Therefore, we designed a bicentric randomized-controlled clinical trial dedicated to elucidate the optimization of treatment expectations using OLPs to reduce preoperative anxiety and to improve postoperative outcomes in gynecological patients. Patients will be randomized into three groups prior to laparoscopic gynecological surgery. The design allows for testing the effects of the OLP versus standard care. In addition, we will test whether the effects of OLP can be enhanced by social observational learning, e.g. via a video presenting information about OLP from a satisfied patient. The primary outcome will be preoperative anxiety. Secondary outcomes will include postoperative visceral and somatic pain, sedation requirements and analgesic consumption. Additionally, the perspectives of patients and healthcare providers on the use of OLPs will be evaluated.

Specific objectives of this study:

Objective 1: To compare preoperative anxiety after standard treatment (TAU-Group) against modulation of treatment expectations using OLP (OLP-Group), and to determine whether the effects after modulation of treatment expectation using OLPs can be enhanced by a video with aspects of verbal suggestion and social learning (OLP+V-Group).Objective 2: To compare dynamic changes in anxiety and treatment expectation over time in the three groups.Objective 3: Comparison of group differences in the pre- and postoperative course, in particular patient-reported visceral and somatic postoperative pain intensity, sedative, anesthesia and analgesic requirements, duration of anesthesia induction and hospital stay.Objective 4: To explore the patients and health care providers perspective regarding the use of OLPs to reduce anxiety before surgery.

## Methods

2

### Setting

2.1

This bicentric study is conducted at the University Hospital Essen, University Duisburg-Essen, Germany and the University Hospital Hamburg-Eppendorf, University of Hamburg, Germany as affiliated project of the Collaborative Research Center (CRC) 289 “Treatment Expectation”, funded by the German Research Foundation (Deutsche Forschungsgemeinschaft, DFG).

The overall goal of the CRC is to elucidate mechanisms and clinical implications of treatment expectations (https://treatment-expectation.de/en/). The present study is accomplished as cooperation as part of the subproject A04 (PI: author [name]) and of the subproject A13 (PI: author [name]). Ethical approval for this study was obtained in coordinated process of the ethics committees at University Hospital Essen (23–11529-KOBO) and Hamburg (2023–200843-BO-kV-bet). This clinical study has been registered in the German Registry for Clinical Studies (DRKS: DRKS00033221). This protocol (Version 1, 10.06.2024) followed the recommendations for the content of a clinical trial protocol; Standard Protocol Items: Recommendations for Interventional Trials (SPIRIT) and the template for intervention description and replication (TIDieR) checklist and guide.

All patients are required to give informed consent and a physical examination is performed before study enrollment.

### Patients and recruitment

2.2

The recruitment goal is to include a total of N=144 female patients with planned gynecology laparoscopy. To this end, women between 18 and 70 years of age and an ASA Classification from I–III are recruited before the surgery in the department of Anesthesiology and Intensive Care Medicine at the University Hospital Essen, Germany and in the department of Anesthesiology at the University Medical Center Hamburg Eppendorf, Hamburg, Germany.

As part of the standardized recruitment process, we review the operating schedules of the hospitals in advance and consult with the respective gynaecology departments regarding potential candidates. Patients are offered participation in the study during the premedication visit. Exclusion criteria include any acute major psychiatric illnesses (severe episodes of anxiety, affective disorders, psychosis, or acute exacerbations of substance abuse), a suspected highly malignant tumor requiring surgery to remove one or more than one organ, benzodiazepines in long-term medication defined as regular daily intake according to the medication plan at least one month, previous serious anesthesia-related complications (e.g. difficult airway with anesthesia problem card), expected difficult airway leading to fiberoptic awake intubation as a particularly anxiety-inducing procedure or rare hereditary galactose intolerance, lactase deficiency or glucose-galactose malabsorption due to the ingredients of the placebo pill. In addition, an insufficient proficiency in the German language and in retrospect severe peri- and postoperative complications (e.g. life-threatening condition with unplanned admission to the intensive care unit or death) leading to exclusion. History of drug use and abuse is taken during the premedication visit and taken into account for our study.

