### Design and groups

2.3

The study design of this bicentric, prospective, randomized, controlled, interventional trial is visualized in **Figure 1**, and procedures are described in detail in subsequent sections. Female patients are randomized into three groups before undergoing gynecological laparoscopic surgery. Randomization is accomplished prior to the personal interview with the study physician. To randomize the patients, we use block randomization with random distribution to ensure a balance in sample size across groups over time and the ability to perform interim analysis. Stratification is performed within the Hamburg and Essen clinic locations.

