### Study procedures

2.4

Patients undergoing elective gynecological laparoscopy at the University Hospitals of Hamburg and Essen are offered to participate in the study. After consultation with an anesthesiologist who is not involved in the study, patients are informed about the study, clinically examined and informed consent is obtained by a study physician, an experienced anesthesiologist. In all groups, information about the study is provided by the study physicians in the premedication outpatient clinics individually, which is typically one to five days before the surgery at both study sites.

Patients are assessed at 5 predefined time points. After informed consent, patients complete a comprehensive questionnaire battery (T1). This package includes information on demographics, state and trait anxiety, pain level over the past 4 weeks, treatment expectations regarding to the upcoming surgery and, if applicable, expectations concerning OLP (for details see 3.5). Patients will complete a short questionnaire at the beginning and at the end of the consultation with the study physician, about their current anxiety and treatment expectations in order to assess the impact of the study physician’s suggestions, including the rationale for OLP. Additionally, the patients rate the warmth and competence of the study physician using a standardized questionnaire. Patients in the OLP+V-Group watch the video after the consultation with the study physician and are also subsequently asked to answer questions about their perception of the video.

At the time the patients are called to the operating room, approximately 45 minutes before the start of surgery (T2), patients randomized to the OLP groups receive OLPs from the nursing staff. In addition, the patients evaluate their preoperative anxiety. Just before the induction of anesthesia in the preoperative phase (T3), preoperative anxiety is assessed again. In addition, the anesthetist subjectively assesses the patients’ level of calmness or anxiety. After surgery in the recovery room, patients are asked about their current level of anxiety and about their current pain level for visceral and somatic pain modalities (T4).

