#### Clinical data

2.5.7

In order to analyze the effects of our intervention on objective measures such as medication requirements and medication intake, we record:

previous illnesses, previous medication the preoperative consumption of sedativesmedication administration and dosage (including hypnotics and analgesics) during induction of anesthesiamedication, especially analgesics in the recovery room and in the post-operative phase

In addition, we record the type of surgery and times relevant in everyday clinical practice with regard to the duration of anesthesia induction, the operation and in the recovery room, as well as the length of hospital stay.

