### Data analysis

2.7

A power analysis calculated with G*Power (version 3.1.9.6) resulted in a sample size of 120 patients for an expected small to medium effect size f of 0.2, two measurement time points, three groups, a significance level of α=0.05 and a power of 0.95. In order to be able to take possible exclusions during the course of the study into account, 20% more patients will be recruited, so that the final sample size is N=144 women. The effect size was derived from our own data and the literature after careful consideration with experts and colleagues at the two university hospitals. A medium to small effect size was chosen in order to be able to investigate small effects.

To analyze the main outcome (object 1), preoperative anxiety (APAIS), we will perform a univariate analysis of variance (ANOVA) with *post hoc* tests to determine differences in anxiety before surgery in the three groups. To analyze the dynamic changes of anxiety in the different groups before and after open placebo administration (TAU, OLP and OLP-V), repeated measures analyses of variance followed by *post hoc* tests are performed (object 2). In addition, ANOVAs will be conducted to assess postoperative pain (NRS) and other clinical characteristics by group (object 3). Patient and staff reports are primarily analyzed descriptively and free-text qualitatively (object 4). Furthermore, correlation and regression analysis will be used to identify exploratory predictive patient characteristics (object 3 & 4). No interim analysis is planned. If data is only available from one patient at three or fewer time points, the patients are excluded from the analysis.

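### Postoperative pain is compared by group alone, without the site stratum or the baseline pain, medication and surgery data the trial collects; the cost is precision, not bias

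*Protocol article*

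**What the plan says.** All references are to the protocol article.

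- **Eligibility (2.2).** The aim is to "include a total of N=144 female patients with planned gynecology laparoscopy". Among the exclusions are "benzodiazepines in long-term medication defined as regular daily intake according to the medication plan at least one month" and "a suspected highly malignant tumor requiring surgery to remove one or more than one organ". No criterion concerns chronic pain or regular analgesic use, and eligible procedures are not divided into classes.
- **Randomisation (2.3).** "Stratification is performed within the Hamburg and Essen clinic locations". No other stratification factor is named.
- **Data recorded.** The T1 battery covers "state and trait anxiety, pain level over the past 4 weeks" (2.4). Under clinical data (2.5.7) the trial collects previous illnesses and previous medication, and "we record the type of surgery and times relevant in everyday clinical practice".
- **Analysis (2.7).** "ANOVAs will be conducted to assess postoperative pain (NRS) and other clinical characteristics by group (object 3"). No covariate or stratum is attached to this comparison. A later sentence adds exploratory correlation and regression to find predictive patient characteristics for objectives 3 and 4.
- **Status of the outcomes.** The introduction lists visceral and somatic pain and analgesic consumption as secondary. Section 3 expects less pain in the OLP groups, treats at least 1 NRS point as clinically relevant, and calls the analgesic analysis exploratory.

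**The concern.** Within the stated criteria, a woman with long-standing pelvic pain and regular analgesics booked for a longer laparoscopic procedure can be randomised alongside a pain-free woman booked for a short one. Such differences exist before surgery and plausibly predict postoperative pain and analgesic use. A by-group ANOVA leaves all of that variation in the error term. It also leaves out site, although site was used to constrain the allocation; if site predicts pain, omitting it makes the test somewhat conservative.

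Two things are at stake. The first is the chance of detecting the 1-point difference that the article itself calls relevant. The second is that, with 40 to 48 women per arm, a chance imbalance in pre-existing pain or procedure stays in the estimate and may look like an OLP effect or mask one.

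**Working it through.** **Arm sizes.** Section 2.7 gives 120 from the power analysis and adds 20%: 120 × 1.2 = 144. Over three groups this is 40 per arm after the allowed losses and 48 at full recruitment. The 120 belongs to a design with two measurement times. The correlation between them is not stated; a group-by-time test with f = 0.2 gives 120 if that correlation is 0.4 (power 0.952). No separate calculation is given for pain.

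**Inputs.** From the article: a 1-point NRS difference, two-sided alpha 0.05, 40 or 48 per arm. Assumed, because the article gives neither: pain SD 2.0 to 2.5, and multiple correlation r of the baseline covariates with postoperative pain of 0.3 to 0.5.

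**Formulae.** Residual SD after adjustment = SD × √(1 − r²). Noncentrality = 1 / (residual SD × √(2/n)). Power comes from the noncentral t distribution with 2n − 2 degrees of freedom, without multiplicity correction. Charging four further degrees of freedom for covariates changes power by less than 0.001.

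Example with SD 2.0 and n = 40: unadjusted noncentrality is 1 / (2.0 × √0.05) = 2.236, power 0.598. With r = 0.5 the residual SD is 2.0 × √0.75 = 1.732, noncentrality 2.582, power 0.722.

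| n per arm | SD | Unadjusted | r = 0.3 | r = 0.4 | r = 0.5 |
|---|---|---|---|---|---|
| 40 | 2.0 | 0.598 | 0.639 | 0.674 | 0.722 |
| 40 | 2.5 | 0.424 | 0.457 | 0.487 | 0.532 |
| 48 | 2.0 | 0.679 | 0.720 | 0.753 | 0.799 |

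With 40 per arm the gain is 4 to 12 points at SD 2.0 and 3 to 11 points at SD 2.5. The equivalent increase in sample size is 1/(1 − r²): 1.10, 1.19 and 1.33, that is 10% to 33%.

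**Three-group test.** At f = 0.2 and N = 120, noncentrality is 0.04 × 120 = 4.8 and power 0.48. Covariates explaining 10% or 20% of the variance raise it to 0.52 or 0.57 (three covariate degrees of freedom).

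**Chance imbalance.** If 30% of women had chronic pain (assumed), two arms of 40 would differ by at least 15 percentage points (6 women) with probability about 0.18.

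**Timing of the covariates.** Allocation precedes consent (2.4.2), the consent form differs by allocation (2.4.1), and T1 is completed after consent (2.4). The T1 pain item therefore predates the pill but not knowledge of the treatment offered. Section 2.5.7 does not say whether the recorded surgery type is planned or performed. Both points constrain the fix.

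**The case against.** The strongest reply is that a covariate list for secondary outcomes normally sits in an analysis plan, and only a condensed article is shown. That would settle the matter if section 2.7 had left the method open. It names a method, and a better one exists on data already collected. If an unshown plan already adjusts, the sentence in 2.7 needs only to say so.

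Several stronger readings are tempting and do not hold:

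- *Eligibility is faulty.* It is not. The primary outcome is preoperative anxiety, and having no pain-related exclusion to match the benzodiazepine one is a legitimate choice.
- *Any laparoscopic procedure is admitted.* Only gynecological laparoscopy is, and suspected highly malignant tumors needing organ removal are excluded.
- *The recorded variables are ignored.* Section 2.7 plans exploratory regression on patient characteristics, and section 2.2 says "History of drug use and abuse is taken during the premedication visit and taken into account for our study". Neither, however, is a stated adjustment of the group comparison.
- *The authors concede the point in 4.1.* They say the postoperative situation may depend on the clinical outcome of the operation. That arises after treatment starts and is not procedure type; their remark on another statistical approach concerns random effects.
- *The comparison is biased.* Randomisation balances these factors in expectation, and the unadjusted test's error rate already allows for chance imbalance.

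It is also fair that the gain is modest and assumed. At r = 0.3 it is 3 to 4 points, and even at r = 0.5 pairwise power stays between 53% and 72% with 40 per arm. The choice of contrast matters as much: pooling both OLP groups against TAU (80 versus 40) gives 73% (SD 2.0) or 54% (SD 2.5) unadjusted.

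**Conclusion.** The point stands as an inexpensive improvement to secondary and exploratory analyses. The stated pain comparison omits the stratification factor and three recorded prognostic variables. The consequence is lost precision and uncorrected chance imbalance, not systematic bias, and the primary anxiety outcome is not touched. With 40 women per arm the loss is about 3 to 12 points of power for a 1-point pairwise difference. This rests on an assumed SD of 2.0 to 2.5 and r of 0.3 to 0.5, neither of which the article supplies; a weaker correlation would make the gain smaller. Adjustment helps but does not by itself make the trial well powered for pain.

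**What to change.** In section 2.7, before unblinding:

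1. Replace the by-group ANOVAs of T4 and T5 pain with ANCOVA on group, site, 4-week pain from T1, and planned procedure class.
2. Define two or three procedure classes before unblinding. Use the planned procedure; if the recorded type is the performed one, take the planned one from the operating schedules that section 2.2 says are reviewed for recruitment.
3. For analgesic consumption, add regular preoperative analgesic use (yes/no), derived from previous medication.
4. State that the T1 pain item recalls the period before enrolment although it is answered after allocation-specific consent, and report the unadjusted or site-only result as a sensitivity analysis.

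No exclusion criterion changes and no new patient questionnaire is needed. The cost is a few degrees of freedom, the work of fixing the procedure classes, and possibly one look-up of the planned procedure per patient.
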